#### Feasibility and Acceptability

Feasibility will be assessed using several descriptive indices. These include the number of participants who complete all 5 intervention sessions (participation rate), average session length (minutes), and days between sessions. To evaluate the ease, usefulness, and impact of the intervention (see Textbox 1), participants will be invited to complete and online survey after the fourth intervention session (T2, Figure 1) to rate their agreement on several acceptability items using a 5-point Likert scale from strongly disagree to strongly agree (eg, “*The Reboot program improved my knowledge about strategies for promoting fruits and vegetables to my child* ”). Items from the task and goal subscales of the Validated Working Alliance Inventory were also included to evaluate participants perceptions of the facilitator (eg, competence) [27].

#### Childhood Cancer Survivors Fruit and Vegetable Intake

To measure CCS fruit and vegetable intake, participants will be invited to complete 2 validated dietary intake assessment methods at baseline (T1), after the fourth intervention session (T2) and 6 months after the fourth intervention session (T3) (see Figure 1). These measures will include the following aspects listed below.

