**Results:**

Reboot is based on an existing, evidence-based parent nutrition intervention and modified for childhood cancer survivors following extensive collaboration with experts in the field. Primary outcomes of feasibility and acceptability will be measured by the number of participants who complete all five sessions, average session length (minutes), length between sessions (days) and parent Likert ratings of the usefulness and impact of the intervention collected after the booster session. Of the 15 participants we aim to recruit, 3 have completed the intervention, 1 declined to participate, 11 are actively completing the intervention and 2 participants are providing written consent. The remaining 3 participants will be recruited via telephone follow-up calls. The intervention is due to be completed by July 2018.

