### Statistical Analyses

Data will be analyzed using the Statistical Package for the Social Sciences, version 18.0 (SPSS Inc, Chicago, IL, USA). The primary outcome measure (number of participants who complete all 5 intervention sessions) will be analyzed using a repeated measures design. An 80% study compliance and 20% attrition rate [18] will be used as the benchmark for program feasibility. Cochran *Q* will be used to identify participants as meeting the specific study completion criterion. The secondary outcome measure is the difference in the mean number of fruit and vegetable serves consumed by CCS (on the previous day) from baseline to the end of the intervention (after the booster session). Paired *t*-tests will be conducted to determine whether there is a significant difference between the mean intakes of fruit and vegetable serves at baseline compared to the end of the intervention.

Postintervention Acceptability Items.

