## Results

Initial planning for Reboot Kids began in 2015 via a collaboration with the developers of the ‘Good for kids: Healthy Habits program’ at the University of Newcastle [15]. Healthy Habits is an evidence-based fruit and vegetable program delivered to nearly 400 Australian families. With their consent, our team updated the original parent guidebook to include the most recent version of the Australian Dietary Guidelines and Nutrition Australia Healthy Eating Pyramid, and dietitian approved recipes. To promote immediate and long-lasting intervention changes, we also followed recommendations by the original developers to focus on parent providing of fruit and vegetables to CCS, which mediated the short-and-long-term effectiveness of the intervention [22]. We therefore modified the initial behavior change technique from parenting self-monitoring of CCS daily fruit and vegetable intake to occasions of parent providing of fruit and vegetables to CCS over three days (Table 1).

Ethics approval was obtained on 11th November 2015 (HREC/15/SCHN/395) and recruitment commenced in August 2016. Of the 20 participants we aim to recruit, 7 have completed the intervention (including the booster session), 1 declined to participate after consenting, 2 participants dropped out after completing the first session, 8 are actively completing the intervention and 3 participants are providing consent. We aim to recruit the remaining participants via telephone follow-up calls and complete the intervention by July 2018.

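### Follow-up is timed by sessions attended and diet is tested on complete pairs, so acceptability and intake change risk describing completers only

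*Protocol article*

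**What the plan says.** The protocol article places its post-baseline measurements as follows.

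- **Diet measures** (Childhood Cancer Survivors Fruit and Vegetable Intake): the recall and the food frequency questionnaire are done at baseline (T1), and then "after the fourth intervention session (T2) and 6 months after the fourth intervention session (T3").
- **Acceptability survey, Methods** (Feasibility and Acceptability): parents get an "online survey after the fourth intervention session (T2, Figure 1) to rate their agreement on several acceptability items".
- **Acceptability survey, Abstract** (Results): the primary outcomes include "parent Likert ratings of the usefulness and impact of the intervention collected after the booster session".
- **Diet analysis** (Statistical Analyses): the change runs "from baseline to the end of the intervention (after the booster session"), and paired "tests will be conducted to determine whether there is a significant difference between the mean intakes of fruit and vegetable serves" at the two points.
- **Attrition:** Recruitment and Statistical Analyses both use 20%. The main Results section reports that "2 participants dropped out after completing the first session".

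None of these sections gives a date counted from enrolment, T1 or session 1 for a parent who does not reach session 4 or the booster.

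**The concern.** Every post-baseline assessment is triggered by a session having taken place. Followed literally, a parent who stops after session 1 reaches neither the trigger for T2 nor the date from which T3 is counted. That parent then gives no acceptability rating and no follow-up intake, and the child drops out of a paired test because one half of the pair is missing.

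This matters most for acceptability. Parents who found the calls too long, inconvenient or irrelevant may be the ones who left, and Textbox 1 asks about exactly those things. If only those who stayed are asked, a high agreement rate partly reflects who was left to answer. The Discussion says that the feasibility and acceptability data will inform a randomised trial. The design is single-group pre-post, so no comparison arm would show or offset such selection. Intake change has the same weakness at the secondary level.

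**Working it through.** **1. When could an early stopper be assessed?**

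| Section | Measure | Trigger | Parent who stops after session 1 |
|---|---|---|---|
| Feasibility and Acceptability | Survey | Session 4 (T2) | No date |
| Abstract, Results | Survey | Booster | No date |
| Childhood Cancer Survivors Fruit and Vegetable Intake | Diet | Session 4 (T2); 6 months after it (T3) | No date |
| Statistical Analyses | Diet change | Booster | No date |

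The gap is present on every reading. The post-booster reading is stricter, because it also loses parents who stop between session 4 and the booster. The booster comes 6 weeks after session 4, so it falls between T2 and T3, and no diet measure is scheduled there. The paired test therefore has no matching follow-up assessment.

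**2. The plan's own figure.** The 20% attrition enters one calculation, the number of parents to contact, given as about 50. Contacts = N / (response × (1 − attrition)).

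- N = 15: 15 / (0.5 × 0.8) = 37.5, so 38. This does not reproduce 50.
- N = 20 (the target in the main Results section): 20 / (0.5 × 0.8) = 50.

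That mismatch is a separate matter. Both targets are carried forward here.

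**3. How many may be missing?**

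- Planned, 20%: 15 × 0.8 = 12 complete pairs, or 20 × 0.8 = 16.
- Observed (main Results section: 7 completed, 2 stopped, 8 active): 2 / (7 + 2) = 22% of those with a known end status, or 2 / (7 + 2 + 8) = 12% of starters so far.

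**4. Acceptability bounds, with no assumption about stoppers' views.** Worst case: all missing parents disagree. Best case: all agree.

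| Starters | Completers agreeing | Worst case | Best case |
|---|---|---|---|
| 15 | 12/12 = 100% | 12/15 = 80% | 15/15 = 100% |
| 15 | 11/12 = 92% | 11/15 = 73% | 14/15 = 93% |
| 20 | 16/16 = 100% | 16/20 = 80% | 20/20 = 100% |
| 20 | 14/16 = 88% | 14/20 = 70% | 18/20 = 90% |

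**5. Size of the overstatement under assumed values.** The documents give no values for stoppers, so these are assumptions shown as a range. Overstatement = d × (completer value − stopper value), where d is the share not assessed.

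| Assumption | d = 12% (2/17) | d = 20% | d = 22% (2/9) |
|---|---|---|---|
| Agreement: completers 90%, stoppers 90% | 0 | 0 | 0 |
| Agreement: completers 90%, stoppers 50% | 4.7 points | 8.0 points | 8.9 points |
| Agreement: completers 90%, stoppers 20% | 8.2 points | 14.0 points | 15.6 points |
| Intake: completers +1.0 serve, stoppers +1.0 | 0 | 0 | 0 |
| Intake: completers +1.0 serve, stoppers 0 | 0.12 serves | 0.20 serves | 0.22 serves |

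If stoppers did better than completers, the sign would reverse.

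**The case against.** A reader might infer that early stoppers will never be asked and that both outcomes are certain to look too good. The documents do not support either inference.

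- **Never asked.** The article says only that participants are invited; it does not bar contact with parents who stop. The flowchart is not shown, and rules for following up withdrawals and handling missing data may be in a fuller document. This stands against the word never. It does not remove the point, because the article states a timing rule, and that rule gives stoppers no date.
- **Favourable bias.** No figure in the documents fixes its sign or size. This stands: the bias needs stoppers to do worse than completers.
- **20% missing at T2.** The article does not say when attrition occurs. A parent lost between session 4 and the booster would still reach T2, so the share missing T2 may be below 20%. This stands, and is why the observed 12% and 22% are shown as well.
- **The paired test belongs to T2 or T3.** It does not: Statistical Analyses sets it after the booster. The selection would then be stricter, and the passages need reconciling.
- **A mixed model would cure this.** It would not. A child with only T1 gives no direct information on change, and the model would rely on data being missing at random. If stoppers do supply follow-up, a paired analysis can include them too.
- **Limited stakes.** The count completing all five sessions, which Statistical Analyses names as the primary outcome measure, treats stoppers as non-completers, so dropout stays visible. Intake is secondary, and the Discussion disclaims definitive efficacy conclusions. This stands and limits the point, but the Abstract also lists acceptability ratings among the primary outcomes.

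**Conclusion.** The point holds as a risk of completer-only results that the plan should remove. Post-baseline outcomes are timed by sessions attended, diet change is tested on complete pairs, and early stopping is both planned for and already seen. The effect falls on acceptability and intake change, not on the five-session completion count.

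If all of the planned 20% loss fell before the assessment, unanimous agreement among 12 completers would be compatible with 80% to 100% of 15 starters, and 11 of 12 with 73% to 93%. Under the assumed scenarios, the overstatement runs from zero to about 16 percentage points for agreement and from zero to about 0.2 serves for intake. A favourable direction is plausible but not established. Separately, the article contradicts itself on whether the end-of-intervention assessment follows session 4 or the booster.

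**What to change.** 1. **Add a fallback date.** Keep session-based timing for parents who reach session 4. For every other parent who started, set T2 and T3 by calendar from T1 or session 1, for example from the day session 4 would have fallen on the weekly schedule. Invite them to the survey and diet measures unless they have withdrawn from data collection. This includes the two who stopped after session 1.
2. **Report over all starters.** Give agreement with all starters as the denominator, show non-responders, and add the best and worst case bounds.
3. **Label the diet result.** Report mean change with a 95% CI from all parents with follow-up, and call it completer-only if stoppers do not respond. A mixed model is optional and does not replace collecting the data.
4. **Reconcile the timing.** The Abstract (Results), Feasibility and Acceptability, Childhood Cancer Survivors Fruit and Vegetable Intake, and Statistical Analyses must agree on whether the end-of-intervention assessment follows session 4 or the booster. If it is the booster, a diet measure has to be scheduled there.

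The cost is a few extra invitations and recall calls by existing staff, plus changes of wording. With 8 parents still active and 3 consenting at the time of writing, the change could still be made. Some stoppers will not respond, and some Textbox 1 items, such as those on the number of sessions or the skills learnt, fit a parent who attended one session poorly.

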### 24-hour Dietary Recall

A 24-hour dietary recall will be conducted by a registered dietitian via telephone [28] to obtain a list of everything the CCS ate and drank during the previous day. This information will be manually entered into FoodWorks 8, an Australian nutrient analysis software (Xyris, Brisbane, QLD, Australia), by a registered dietitian to produce a calculation of total daily fruit and total daily vegetable servings for each child [29]. Intake (total fruit and total vegetable servings consumed) will also be used to categorize CCS as meeting (or not meeting) the recommended daily intake for fruit and vegetables, separately, for their age.

### Food Frequency Questionnaire

The fruit and vegetable subscales scores from the Australian Child and Adolescent Eating Survey, a brief (15 minutes) online FFQ, will be used to provide quantitative data on the number of daily fruit and vegetable serves for age and variety of fruit and vegetables consumed [30-32] where a higher fruit (out of 12) and vegetable variety score (out of 21) indicates greater intake of a variety of fruit and vegetables [33].

### Statistical Analyses

Data will be analyzed using the Statistical Package for the Social Sciences, version 18.0 (SPSS Inc, Chicago, IL, USA). The primary outcome measure (number of participants who complete all 5 intervention sessions) will be analyzed using a repeated measures design. An 80% study compliance and 20% attrition rate [18] will be used as the benchmark for program feasibility. Cochran *Q* will be used to identify participants as meeting the specific study completion criterion. The secondary outcome measure is the difference in the mean number of fruit and vegetable serves consumed by CCS (on the previous day) from baseline to the end of the intervention (after the booster session). Paired *t*-tests will be conducted to determine whether there is a significant difference between the mean intakes of fruit and vegetable serves at baseline compared to the end of the intervention.

Postintervention Acceptability Items.

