## Methods

### Recruitment

We aim to recruit the parents of 15 CCS. This number is sufficient to provide exploratory findings to inform the design of a randomized controlled trial (RCT) in this population [18]. Based on our previous research, we assume a response rate of 50% and attrition rate of 20% [18-20], and therefore it was anticipated that approximately 50 parents will need to be contacted to recruit 15 families.

Parents will be eligible to participate if they have a child aged between 2-12 years who completed cancer treatment at the Sydney Children’s Hospital (SCH), Randwick, NSW, with curative intent, achieved remission less than 5 years ago and meet the following criteria which are (1) to provide informed consent, (2) be able to read English, and (3) have regular telephone access. Parents will be ineligible if they have (1) insufficient English language skills to complete telephone sessions and or baseline and follow-up assessments, (2) severe depression or suicidal ideation, as determined by the clinical experience of the treating oncologist, or if their child who had cancer, (3) is currently on active treatment or receiving supplementary feeding, (4) has relapsed, (5) is in palliative care or is deceased, or (6) completed cancer treatment more than five years ago.

Eligible participants will be recruited via mail using an information and consent form explaining the purpose of the project and details of participation. Participants can choose to participate by returning the consent form or by contacting the study coordinator. Nonrespondents will be contacted by study personnel via telephone or text message. This protocol was approved by the Network Human Research Ethics Committee (HREC/15/SCHN/395).

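### Cochran Q and a repeated-measures design are the wrong method for the primary feasibility outcome, which is one completion proportion set against an 80% benchmark

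*Protocol article*

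**What the plan says.** The Statistical Analyses section identifies the primary outcome as the count of participants who finish all five sessions (four weekly sessions plus the booster) and says it "will be analyzed using a repeated measures design". It then gives the criterion: "An 80% study compliance and 20% attrition rate [18] will be used as the benchmark for program feasibility". The next sentence says that Cochran Q "will be used to identify participants as meeting the specific study completion criterion".

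The Feasibility and Acceptability section treats the same count, there called the participation rate, in simpler terms: "Feasibility will be assessed using several descriptive indices". The abstract also lists the count among the feasibility measures.

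Two further statements bear on the remedy. Under Recruitment the target is given as "We aim to recruit the parents of 15 CCS", whereas the Results section gives a target of 20 and reports one person who declined after consenting and two who left after the first session. The Discussion describes the study as a pre-post intervention, and no comparison group is mentioned.

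**The concern.** A parent either completes all five sessions or does not. That gives one binary value per parent, in one group, with a fixed external benchmark, so the quantity of interest is a single proportion. Cochran Q is designed for several binary measurements on each subject, and its null hypothesis is that the success proportion is the same under every condition. It does not do what the sentence asks of it, which is to identify participants who meet a criterion, and it has no place for a reference value of 80%.

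Feasibility is the pilot's main aim, and its results are meant to inform a randomized trial. If the named method is followed and a Q statistic is reported beside the primary outcome, readers may take it as evidence about feasibility when it carries none.

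**Working it through.** **Inputs.** Five sessions, completion of all five as the outcome, and the 80% compliance benchmark come from the Statistical Analyses section. The target of 15 comes from Recruitment and that of 20 from Results. The document gives no numerical result for the primary analysis to reproduce. All attendance tables below are illustrative assumptions, not trial data.

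**Formula.** With k columns, column totals C, row (parent) totals R and grand total T:

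Q = (k − 1)[k ΣC² − T²] / [k T − ΣR²], on k − 1 degrees of freedom.

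**Step 1: the outcome as defined (k = 1).** The factor k − 1 is 0, and because each R is 0 or 1, kT − ΣR² = T − T = 0. Q is 0/0.

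**Step 2: the charitable reading, attendance at each of five sessions (k = 5), 15 parents.**

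- 12 complete and 3 stop after session 1 (80%, benchmark met). Column totals are 15, 12, 12, 12, 12, so T = 63, ΣC² = 225 + 4 × 144 = 801 and ΣR² = 12 × 25 + 3 × 1 = 303. Q = 4(5 × 801 − 63²)/(5 × 63 − 303) = 4(4005 − 3969)/12 = 144/12 = 12.0, 4 df, p = 0.017 by the chi-square approximation. Only three rows are informative. The exact permutation p is 5 × (1/5)³ = 0.04.
- 10 complete and 5 each miss a different session (67%, benchmark missed). Every column total is 14, T = 70 and ΣR² = 10 × 25 + 5 × 16 = 330. Q = 4(5 × 980 − 4900)/(350 − 330) = 0/20 = 0, p = 1.
- 9 complete and 6 never start (60%, benchmark missed). kT = 5 × 45 = 225 and ΣR² = 9 × 25 = 225. Q is 0/0.
- All 15 complete. kT = 375 and ΣR² = 15 × 25 = 375. Q is again 0/0.

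**Step 3: completers do not enter the statistic.** A parent who attends all five adds 5 × 5 − 5² = 0 to the denominator and adds the same constant to every column, which leaves the numerator unchanged. To see the effect, hold three non-completers fixed (two leaving after session 1, one after session 3) and vary the number of completers. For 12 completers the columns are 15, 13, 13, 12, 12, so Q = 4(5 × 851 − 65²)/(325 − 311) = 120/14 = 8.57, p = 0.073. The value is identical for 3/6 (50%), 7/10 (70%), 12/15 (80%), 17/20 (85%) and 97/100 (97%) completing.

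**Step 4: the quantity the benchmark needs.**

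| Completers | Proportion | Exact 95% CI | Wilson 95% CI |
|---|---|---|---|
| 12/15 | 80% | 51.9% to 95.7% | 54.8% to 93.0% |
| 16/20 | 80% | 56.3% to 94.3% | 58.4% to 91.9% |

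The observed proportion reaches 80% by chance fairly often. With 15 parents, the probability of at least 12 completers is 0.30 if true completion is 70% and 0.65 if it is 80%. With 20 parents and a mark of 16, the probabilities are 0.24 and 0.63.

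**Step 5: the denominator matters.** Suppose 12 of 15 parents who start complete, and one more consents but declines before starting. Then 12/15 = 80% meets the mark, but 12/16 = 75% does not.

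**The case against.** The strongest defence is that the sentence is a garbled addition to an otherwise usable plan. The outcome is named as a count, the benchmark is stated, and the Feasibility and Acceptability section describes the index as descriptive. Anyone can count completers, divide and compare with 80%. Five attendance indicators per parent are also genuine repeated binary data, for which Q is a recognised test of changing attendance. All of this is fair, and it limits the consequence. It does not make the named method suitable for the outcome it is attached to.

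Three stronger readings are tempting, but the document does not support them:

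- A reader might infer that the pilot's primary question cannot be answered. It can be, from the stated count and benchmark, without using Q.
- A reader might infer that a Q p-value could overturn the benchmark. The document gives no hypothesis, significance level or p-value rule for Q. The only stated feasibility criterion is the 80%/20% benchmark, so nothing formally competes with it. The risk is one of misreading a reported Q.
- A reader might see a contradiction between the two Methods sections. An index can be reported descriptively and also carry a test, so this is a mismatch in emphasis, not a strict contradiction.

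Nor is the absence of a named confidence interval a fault in itself. A condensed article may leave that to a fuller document. The fault is the method that is stated.

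**Conclusion.** The point holds in a limited form: the article names an unsuitable method for its primary outcome. On the definition given, Q is undefined. On the charitable session-by-session reading, it tests whether attendance differs between sessions, discards all full completers, and took the same value for completion anywhere from 50% to 97% in the worked example. The algebra does not depend on the trial's data. The particular Q values rest on assumed attendance tables, and p = 0.017 rests on a chi-square approximation with three informative rows.

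The consequence is moderate. Feasibility can still be judged from the count and the benchmark, but a Q result presented as the primary analysis would be uninformative at best and could mislead the decision about the later trial. This should be fixed before analysis. It does not undermine the pilot.

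**What to change.** In the Statistical Analyses section, delete the repeated-measures design and Cochran Q for the primary outcome. Replace them with wording such as: the primary feasibility outcome is the number and proportion of enrolled parents who complete all five sessions, reported with an exact (Clopper-Pearson) or Wilson 95% confidence interval and compared descriptively with the 80% benchmark.

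Two details need to be settled alongside this:

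- State the denominator, including how a parent who consents and then declines is counted, since the Results section already reports one.
- Reconcile the target of 15 with that of 20, then give the pass mark as a count (12 of 15, or 16 of 20).

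If attendance over time is of interest, a simple table of numbers attending each session is enough.

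The cost is about two sentences and no new data. The drawback is that the interval will be visibly wide (about 52% to 96% at 12/15, or 56% to 94% at 16/20), which is a reason to use the benchmark as a descriptive guide and not as a hypothesis test.

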**Objective:**

This pilot study aims to assess the feasibility and acceptability of delivering evidence-based telephone support to parents of childhood cancer survivors. A secondary aim includes assessing the effect of Reboot on improving childhood cancer survivors’ dietary quality by increasing child fruit and vegetable intake and variety and its contribution to overall nutrient intake.

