## Discussion

This paper outlines the protocol for a pre-post, parent-led behavioral nutrition intervention for CCS, previously evaluated in a non-cancer pediatric population [15,16]. Although interventions piloted in non-cancer pediatric populations have led to significant increases in child fruit and vegetable intake [16], there is no research on their effectiveness in this high-risk population of CCS [34]; highlighting the unique contribution of the Reboot program [35].

We anticipate that the multimodal approach used in Reboot, encompassing a written parent guidebook and semi-structured telephone calls will contribute to the aim of the study. Telephone contact as the primary mode of intervention delivery can be efficacious [36], providing parents with support from a healthcare professional without requiring travel [12]. This flexibility is important in ensuring equitable access to families of CCS living in rural and regional areas [12]. Parents of CCS also report a preference for workbooks which provide relevant information about their children’s health after treatment [12].

The number of intervention contacts is also known to moderate intervention effectiveness, with behavior change often requiring multiple points of contact [37]. Booster sessions are often recommended to reinforce or re-establish messages or behavior changes suggested during interventions [38]. Subsequently, we chose to modify the original intervention to include 1 booster session. However, there is no research on the impact of booster sessions in dietary interventions in CCS. Moreover, the effectiveness [38] and optimum timing [39] of booster sessions in the wider behavior change literature is also unclear [40]. Most studies suggest that booster sessions should be instituted within three months after the intervention is complete to maximize efficacy [38,39], supporting our design of a booster session at 6 weeks post-intervention.

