The Reboot study design has both strengths and limitations. As a pilot study, the small sample size will limit the ability to draw definitive conclusions regarding the efficacy of the intervention in increasing fruit and vegetable intake among CCS. The study will, however, be most useful in assessing the feasibility and acceptability of delivering a behavioral nutrition intervention in this population (Textbox 1). The inherent vulnerabilities of using parent-report as a proxy for child intake also warrants consideration [41]. A recent study indicated that repeated 24-hour recalls were a more valid measurement of dietary intake in CCS compared with FFQs, which underestimated energy intake [28]. However, due to the participant burden of multiple 24-hour recalls [42], we aimed to reduce potential bias in intake measurement by using a single 3-pass 24-hour recall and a validated, parent-administered online FFQ.

The increasing use, and success, of technology-based, parent-led interventions in improving children’s fruit and vegetable intake [43] suggests that online or smart-phone delivered interventions may offer a cost-effective alternative to telephone-based behavior change support [44-46]. Alternatively, online or mobile phone interventions delivered together with minimal telephone support or text messaging, may also help to maintain important human interaction [47] whilst still reducing intervention delivery costs. Given the absence of evidence-based dietary interventions in CCS [48], experimentation with different modes of delivery is an important next step in identifying the most efficacious method for promoting healthy eating habits in this vulnerable population [47].

Subsequently, a future goal of this pilot study is to utilize our feasibility and acceptability data to inform the development of a randomized control trial to evaluate the efficacy of delivering reboot online via web-based modules with brief telephone support (15 minutes) to reinforce key messages, on CCS dietary intake, compared with a wait-list control. If successful, data obtained from the RCT will be used to support the implementation of Reboot by community organizations across Australia, especially those in rural and remote areas, where CCS have poorer access to preventive health care [49].

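### The secondary aim is worded as an effect of Reboot, but an uncontrolled paired test can show only change, and the tested time point matches no scheduled dietary visit

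*Protocol article*

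**What the plan says.** - **Aim.** The Objective in the Abstract lists a secondary aim of "assessing the effect of Reboot on improving childhood cancer survivors’ dietary quality".
- **Design.** The Discussion opens with "This paper outlines the protocol for a pre-post, parent-led behavioral nutrition intervention for CCS". No comparison group is described anywhere in the article.
- **Endpoint and test.** Statistical Analyses defines the secondary outcome as the difference in mean serves on the previous day, "from baseline to the end of the intervention (after the booster session". It then says that paired t-tests "will be conducted to determine whether there is a significant difference between the mean intakes of fruit and vegetable serves at baseline compared" with the end of the intervention.
- **Dietary visits.** The section on fruit and vegetable intake schedules assessments at baseline (T1), "after the fourth intervention session (T2) and 6 months after the fourth intervention session (T3". The Intervention section puts the booster six weeks after session 4.
- **Stated caveat.** The Discussion says that "the small sample size will limit the ability to draw definitive conclusions regarding the efficacy of the intervention". The same paragraph separately notes the weaknesses of parent report and of a single 24-hour recall. It does not mention the absence of a control group.

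**The concern.** The aim asks about an effect, while the analysis answers a different question: whether mean intake differs between two times. The two coincide only if intake would have stayed level without Reboot, and the article's own background makes that doubtful. It describes disrupted eating during treatment, with appetite loss, taste changes, food aversions and steroid use. It then enrols children aged 2 to 12 who have finished treatment within the last five years. Their intake may drift as they recover and grow. The parents who report intake are also the parents being coached.

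A reader told only that sample size limits the efficacy conclusion may think that a significant result, or a larger pre-post study, would settle the matter. It would not.

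Two further points affect what the result will mean. The time being tested is unclear. The paired test also uses only children with both assessments, although 20% attrition is planned for and two participants have already left after session 1.

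**Working it through.** **1. Time point.** Set in order, the schedule is: T1 at baseline; session 4; T2 after session 4; booster six weeks after session 4; T3 six months after session 4. The tested time is after the booster.

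- Read literally, T3 is the only scheduled dietary visit after the booster. It falls months later, and T2 then has no stated analysis.
- Read as the end of the weekly sessions, T2 is meant. It precedes the booster, and T3 then has no stated analysis.

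On either reading the two sections disagree. The study flowchart (Figure 1) could not be seen for this review and may show which is intended, but the text still needs to agree with itself.

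**2. Number of pairs.** The article states no power, SD or target difference for the paired test, so there is no figure of that kind to reproduce. The only sample-size figure is about 50 contacts, at 50% response and 20% attrition:

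- Target 15 (Abstract, Recruitment): 15 / (0.5 × 0.8) = 37.5, not 50.
- Target 20 (Results): 20 / (0.5 × 0.8) = 50.

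Both targets are therefore carried forward. Pairs after 20% attrition: 15 × 0.8 = 12, or 20 × 0.8 = 16.

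**3. Precision and power.** Two-sided 5% is assumed, since the article does not state it. Units are SDs of the within-child change.

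- 95% CI half-width = t(0.975, n − 1) / √n.
- Power comes from the noncentral t with n − 1 degrees of freedom and noncentrality d√n, where d is the mean change in SD units.

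| Pairs | Half-width | d for 80% power | P(significant), d = 0.2 | d = 0.3 | d = 0.5 |
|---|---|---|---|---|---|
| 12 | 0.635 | 0.889 | 0.097 | 0.158 | 0.353 |
| 15 | 0.554 | 0.778 | 0.112 | 0.192 | 0.438 |
| 16 | 0.533 | 0.749 | 0.116 | 0.203 | 0.465 |
| 20 | 0.468 | 0.660 | 0.136 | 0.247 | 0.565 |

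The last three columns can be read in two ways.

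- *As power:* with 12 pairs, a true change of 0.5 SD would be missed with probability 1 − 0.353 = 0.647.
- *As false attribution:* if Reboot has no effect and d is purely background drift, these are the chances of a significant result that might be credited to the programme. They rise with the number of pairs, so a larger sample does not address the missing control group. The drift values are assumptions; the article gives none.

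**4. Restriction to pairs.** In an illustrative simulation there were 15 children and no true change, and the three with the lowest baseline were lost. The mean paired change was biased by −0.23, −0.16 and −0.10 baseline SD for baseline to follow-up correlations of 0.3, 0.5 and 0.7. A regression estimate using all 15 baselines was about unbiased. By symmetry, losing the three highest baselines would reverse the sign. The article does not say who will be lost, so the direction of any bias is unknown.

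**The case against.** The strongest reply is that this is an openly labelled pilot. Recruitment calls the findings exploratory, and the Discussion calls the design pre-post, limits definitive efficacy conclusions and leaves efficacy to a later randomised trial with a wait-list control. The t-test sentence asks only whether two means differ, which a paired t-test answers validly. A mixed model cannot supply a control group. All of this is fair and makes the point less serious. It does not remove the mismatch between an aim phrased as an effect and a test of change, or the gap in the stated limitations.

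Several stronger readings are tempting but not supported:

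- *That T3 is unused.* Taken literally, T3 may be the very visit tested. What is established is that the two sections do not match.
- *That the article already claims efficacy.* It plans to assess an effect and hedges the conclusion.
- *That sample size is the only limitation given.* Parent report and recall are acknowledged too; the control group is what is missing.
- *That the analysis covers only programme completers and so favours families who were helped.* The test needs two dietary assessments, not five sessions. The article does not say that early leavers will have no follow-up recall. A missing-data rule may sit in a fuller document.
- *That a paired t-test cannot provide what the later trial needs.* Mean change, its SD and a CI come from the same calculation. The issue is which result the plan puts first.

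**Conclusion.** The point holds in a limited form. The design and the one stated analysis can estimate change in fruit and vegetable serves; they cannot show an effect of Reboot, and the limitations should say so. The time point of the secondary endpoint conflicts with the dietary visit schedule and must be reconciled.

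On size, 12 to 16 pairs give a 95% CI half-width of about 0.64 to 0.53 SD of the change, and 80% power only for changes of about 0.89 to 0.75 SD. Non-significance would therefore be uninformative, while significance could reflect background drift. These figures assume a two-sided 5% level and 20% attrition from a target of 15 or 20. This is a worthwhile improvement to a secondary analysis and not a threat to the study's main purpose.

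**What to change.** 1. Reword the secondary aim as estimating the pre-post change in fruit and vegetable serves, with no efficacy claim.
2. Add the lack of a control group to the limitations, separately from sample size.
3. Reconcile the endpoint time in Statistical Analyses with the dietary visit schedule, naming the visit by its label.
4. Make mean change, SD of change and 95% CI the stated result, separately at T2 and T3, using all participants with any assessment. A linear mixed model with visit (T1, T2, T3) as a factor would do this. Keep the paired difference as a descriptive check.

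The cost is some rewording and a little more analysis of data already being collected. The downside is a more modest claim.
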